### Ethical aspects of the study

The study will be conducted in accordance with the principles of the Helsinki Declaration, as revised and updated, and will follow Spain’s best practice guidelines (*Buena Práctica Clínica*). The protocol was evaluated by our institute’s ethics committee (*Comité Ético de Investigación Clínica [CEIC], Institut d’Investigació en Atenció Primària [IDIAP] Jordi Gol*). Data confidentiality will be protected under the Spanish law governing the protection of personal data (Ley orgánica de Protección de Datos de Carácter Personal (15/1999 13 December).

## Discussion

The development of the proposed smartphone app, and subsequent evaluation of its effectiveness in our population, has the potential to contribute a useful tool for the smoking cessation efforts of young adults, as well as providing information about the effectiveness of smoking cessation interventions in a population that has not been studied in our environment.

A limitation of the study is its open character. Both patients and health care professionals will know that they are involved in the intervention, which might create a bias. The analysis will be blind, with no identifiers available to the statistician that would indicate whether a subject was assigned to the intervention or control group. The study will use random clustering of primary care centres to avoid the risk of contamination by taking geography into account.

The randomization process is intended to result in a balanced distribution of sociodemographic and cultural characteristics between intervention and control groups, both for doctors and nurses and for participating patients. To avoid contamination between the intervention and control groups, the game and the app itself will only be made available to the intervention group. Multivariate analysis will be used to control for possible confounding factors.

Another limitation is the difficulty of recruiting young patients who want to stop smoking. The multicentre study design, with 22 participating primary care centres and a long (18-month) recruitment period, is intended to ensure an adequate participant pool.

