### Sample size/power calculation

To calculate sample size for each primary care centre, the number of individuals in a simple randomized design was multiplied by the design effect. Accepting an alpha risk of 0.05 and a beta risk of 20% in a bilateral contrast, 222 subjects are required in each group to detect a difference of at least 5% (calculations based on EPIDAT v. 3.1). To calculate design effect, we estimated the intracluster correlation coefficient (ICC) in clinical trials randomized by primary care clusters, generally less than 0.05 [12], and as a cluster size. The average size is 20 with a design effect of 1.36. Assuming these values, the definitive sample size for the study was set at 604 subjects, randomised as described above.

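### The 604 subjects assume centres averaging 20, but the 22 centres named would need about 27.5 each, which lowers power from 80% to about 76% at the plan's implied ICC

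*Protocol article*

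**What the plan says.** In the protocol article, Sample size/power calculation, the error rates are set first: "Accepting an alpha risk of 0.05 and a beta risk of 20% in a bilateral contrast". On that basis "222 subjects are required in each group to detect a difference of at least 5" per cent. To allow for clustering, "the number of individuals in a simple randomized design was multiplied by the design effect". The ICC behind that step is given only as a range: "we estimated the intracluster correlation coefficient (ICC) in clinical trials randomized by primary care clusters, generally less than 0.05". The cluster size and inflation factor follow: "The average size is 20 with a design effect of 1.36". The result is that "the definitive sample size for the study was set at 604 subjects".

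Under Randomisation, the primary care centre is the unit, allocated 1:1. The number of centres appears only in the Discussion, as the answer to the difficulty of recruiting young smokers: "The multicentre study design, with 22 participating primary care centres and a long (18-month) recruitment period".

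**The concern.** The total, the average cluster size and the number of centres are tied together: any two fix the third. Here all three are printed and they disagree. This affects more than presentation, because the design effect depends on cluster size. The 1.36 belongs to centres of 20. If 22 centres deliver 604 subjects, the clusters are larger, the design effect is larger for any ICC above zero, and the same 604 subjects carry less information than planned. If instead the centres deliver 20 each, the total falls well short. The stated 80% power is therefore in question either way, and the Discussion relies on the 22 centres to secure enough participants.

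**Working it through.** **Inputs.** From Sample size/power calculation: 222 per group, two-sided alpha 0.05, power 80%, average cluster m = 20, design effect (DE) 1.36, total 604. From the Discussion: 22 centres. The exact ICC is not stated.

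**1. The plan's own total.** N = 2 × 222 × 1.36 = 603.84, so 604. The figure reproduces, which confirms that 1.36, and hence the cluster of 20, was the factor used.

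**2. Centres against total.**
- 22 × 20 = 440, which is 164 short of 604 (440/604 = 73%).
- 604/22 = 27.45 per centre.
- 604/20 = 30.2, so at least 31 centres of 20, or 32 for equal arms.

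**3. Implied ICC.** DE = 1 + (m − 1) × ICC. With DE = 1.36 and m = 20, ICC = 0.36/19 = 0.0189.

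**4. Design effect at the cluster size that 22 centres require.** DE = 1 + 26.45 × 0.0189 = 1.50. Effective n per arm = 302/1.50 = about 201, against 222 planned.

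**5. Power.** I take 222 per arm as giving 80% power and scale by a normal approximation: power = Φ(2.80 × √(n_eff/222) − 1.96), where 2.80 = 1.96 + 0.84.

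| Scenario | ICC | DE | Effective n per arm | Power |
|---|---|---|---|---|
| 604 in clusters of 20 (as planned) | 0.0189 | 1.36 | 222 | 80% |
| 604 in 22 centres (27.45 each) | 0.0189 | 1.50 | 201 | 76% |
| 440 in 22 centres (20 each) | 0.0189 | 1.36 | 162 | 67% |

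**6. Separate sensitivity at ICC 0.05,** the upper end of the range the article cites.
- 604 in clusters of 20: DE = 1 + 19 × 0.05 = 1.95, effective n = 302/1.95 = 155, power about 65%.
- 604 in 22 centres: DE = 1 + 26.45 × 0.05 = 2.32, effective n = 302/2.32 = 130, power about 57%.

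The fall from 80% to 65% comes from the higher ICC alone. Only the step from 65% to 57% comes from the number of centres.

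**7. The ICC at which nothing is lost.** DE at 27.45 per centre stays at or below 1.36 when ICC ≤ 0.36/26.45 = 0.0136.

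**8. What 22 centres would need for 80% at ICC 0.0189.** Solve N = 444 × [1 + (N/22 − 1) × ICC]: N = 444 × (1 − 0.0189)/(1 − 444 × 0.0189/22) = about 705 to 706, about 32 per centre, with DE about 1.59.

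**The case against.** The number 22 is not an input to the sample size calculation. It stands in a Discussion sentence about recruitment, and 604 follows correctly from its own inputs. That is right: this is a mismatch between two sections, not a slip in computing 604. It does not remove the conflict, since the centres are the clusters and the article names no other number of them. Reading 22 as a count per arm does not help: the sentence does not say so, and 44 × 20 = 880 does not match 604 either. Reading 20 as only an average does not help, because 22 centres averaging 20 still total 440.

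Three stronger readings are tempting, and the document does not support them.

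- **That the trial will stop at 440.** The Intervention section ends recruitment at a required quota, but does not say that the quota is per centre or that it is 20. It can equally mean the trial total, and 604 is the stated target. The 67% is conditional on a shortfall that the article does not plan.
- **That the mismatch takes power down to 57%.** That figure needs an ICC of 0.05, which the article gives as a value that ICCs generally fall below. Most of the loss there arises even with centres of 20.
- **That 80% power is missed whatever the ICC.** The 0.019 is back-calculated. At 0.0136 or below, which the cited range allows, a design effect of 1.36 still covers 27.45 per centre.

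**Conclusion.** The inconsistency stands: 22 centres, an average of 20 and a total of 604 cannot all hold, and no part of the article reconciles them. With the 604 recruited from 22 centres, the consequence at the plan's implied ICC is modest, about 4 percentage points of power.

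That size rests on three assumptions: the ICC of about 0.019 recovered from the plan's own design effect, roughly equal centre sizes, and 222 per arm being right for 80% power before clustering. The direction (a design effect above that for centres of 20) holds for any positive ICC; whether the stated power is actually missed depends on an ICC that the article does not pin down. This should be corrected, but it does not by itself undermine the design.

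**What to change.** State the single ICC used, then give one consistent set of number of centres, average cluster size, design effect, total and power, with the same figures in the sample size section and the Discussion. The options at ICC 0.019 are:

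- **Keep 22 centres and 604 subjects.** State 27 to 28 per centre, a design effect of about 1.50 and power of about 76%. The cost is a text correction and a slightly less favourable stated power.
- **Keep clusters of 20 and 80% power.** State 31 centres, or 32 for equal arms. The cost is 9 or 10 more centres.
- **Keep 22 centres and 80% power.** State about 706 subjects, about 32 per centre. The cost is about 102 more participants (706 − 604) in a population that the Discussion already calls hard to recruit.

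Whichever is chosen, say in the Intervention section that the recruitment quota refers to the trial total (604 if that is kept), so that 20 is not taken as a limit per centre. If the sponsor wishes to show robustness to a higher ICC such as 0.05, present it as a separate sensitivity and not as an effect of the number of centres.

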#### Randomisation

The unit of randomisation will be the primary care centre, stratified according to urban/rural location and number of participating professionals to ensure comparability between the study groups, and then assigned 1:1 to the intervention or control group. Randomisation will use the Epidat 3.0 programme.

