### Statistical analysis

Analysis will be performed as intention to treat. At baseline, the comparability of the intervention and control groups will be assessed. Quantitative variables will be described as the mean and standard deviation if they have a normal distribution, or median and range, as appropriate. Qualitative variables will be described as percentages and confidence intervals. Quantitative baseline characteristics will be compared using Student t test. Qualitative variables will use the Pearson chi squared test.

Multi-level multivariate survival analysis will include two effects (fixed and random). The fixed component of the adjusted model will include the group assignment and a dummy variable for baseline and 12-month measurements of the study variables, as well as interactions between relevant variables. All significant covariates in the bivariate analyses (p< 0.30) will be included in the model. This strategy will sufficiently reduce the probability of leaving relevant variables out of the model.

The primary response variable will be continued abstinence at 12 months after beginning smoking cessation (D-Day). We will use multiple techniques to deal with missing values in covariates that are candidates for inclusion in multi-level models. The ’ICE” programme of the STATA-10.1 package estimates missing values by conditional logistic regression, concatenating them with the variables that have complete values. As a convention, a combination of 10 different estimates will be used that includes the variability of these estimates. This will preclude a loss of power due to missing data. In addition, analysis of the models will be repeated to determine sensitivity, using only the subjects for whom complete data are available.

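### The 80% power does not hold for 604 patients in 22 centres: on the protocol's own inputs it is about 76% with normal quantiles and about 72% with t on 20 degrees of freedom

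*Protocol article*

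**What the plan says.** The Sample size/power calculation section sets the error rates: "Accepting an alpha risk of 0.05 and a beta risk of 20% in a bilateral contrast". Its starting figure is that "222 subjects are required in each group to detect a difference of at least 5" percentage points, obtained as for individual randomisation. For clustering it cites an ICC that is "generally less than 0.05" and then gives the inflation: "The average size is 20 with a design effect of 1.36". From these, "the definitive sample size for the study was set at 604 subjects".

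The Randomisation section makes the centre the unit: "The unit of randomisation will be the primary care centre, stratified according to urban/rural location and number of participating professionals", allocated 1:1. The number of centres appears only in the Discussion, which describes a multicentre design "with 22 participating primary care centres".

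On the analysis, the Statistical analysis section says: "Multi-level multivariate survival analysis will include two effects (fixed and random"). It does not say whether the arm effect is referred to a normal or a t distribution, or how degrees of freedom are obtained.

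**The concern.** Two things in the power statement do not match the design.

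- **Centre size.** The design effect is calculated for 20 patients per centre, but 604 patients in 22 centres is about 27.5 each. Larger centres mean a larger design effect, so each patient contributes less information than was assumed.
- **Number of centres.** Multiplying an individually randomised sample size by a design effect takes no account of how many centres are randomised. The arm effect is a comparison between about 11 centres and about 11 others, so its variance is estimated with at most 20 degrees of freedom. A test that respects this needs a larger critical value than 1.96 and has less power. A test that ignores it rejects too often under the null.

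The effect sought is small. If readers believe that power was 80%, a null result will be taken as stronger evidence against the app than it is.

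**Working it through.** **Inputs.** From the Sample size/power calculation section: two-sided alpha 0.05, power 80%, 222 per group, 20 per centre, design effect 1.36, total 604. From the Discussion: 22 centres. From the Randomisation section: 1:1 allocation of centres. I assume equal centre sizes and 11 centres per arm.

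**1. Reproduce the plan's figure.** 2 × 222 × 1.36 = 603.84, which rounds to 604. The number of centres does not enter.

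**2. Implied ICC.** Design effect = 1 + (m − 1) × ICC, so ICC = (1.36 − 1) / (20 − 1) = 0.0189. At the quoted bound of 0.05, the same formula gives 1 + 19 × 0.05 = 1.95.

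**3. Check the counts.** 604 / 22 = 27.45 per centre. 22 × 20 = 440 patients. 604 / 20 = 30.2 centres.

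**4. Degrees of freedom alone, keeping 1.36.** 80% power corresponds to a noncentrality of 1.960 + 0.842 = 2.80.

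- t test on 22 − 2 = 20 degrees of freedom (critical value 2.086): power 76.0%.
- 18 or 16 degrees of freedom, as could follow from stratification terms or centre-level covariates: 75.5% and 74.9%.
- The 30 centres that 20 per centre would imply (28 degrees of freedom): 77.2%.

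**5. Centre size as well.** At 27.45 per centre and ICC 0.0189, the design effect is 1 + 26.45 × 0.0189 = 1.50. The effective number per arm is 604 / 1.50 / 2 ≈ 201, and the noncentrality is 2.80 × √(201 / 222) = 2.67. Normal-quantile power is Φ(2.67 − 1.96) = 76.0%; with t(20) it is 71.8%.

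**6. Range over the ICC, 604 patients in 22 centres.**

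| ICC | Design effect | Power, normal | Power, t(20) |
|---|---|---|---|
| 0.01 | 1.26 | 82.8% | 78.9% |
| 0.019 (implied) | 1.50 | 76.0% | 71.8% |
| 0.03 | 1.79 | 68.4% | 64.1% |
| 0.05 (quoted bound) | 2.32 | 57.3% | 53.2% |

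If instead 20 per centre is kept, 440 patients at design effect 1.36 give 66.7% (normal) or 62.4% (t(20)).

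**7. If the test used 1.96 without correction.** P(|t(20)| > 1.96) = 6.4%, and 6.6% on 18 degrees of freedom. Power at noncentrality 2.80 would then be 79.6%, so this case replaces the t-quantile loss in step 4.

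**8. Dependence on 222.** No control rate is given. A standard two-proportion calculation returns 222 only near 1.2% versus 6.2%. The one 5-point contrast in the Background, 9% versus 4%, is not declared as a design input. It would need 381 per group, and 222 per group would have about 57% power for it before any clustering.

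**The case against.** The strongest objection is that the protocol nowhere says that the arm effect will be tested against a normal distribution. The degrees-of-freedom rule for a multilevel model is the kind of detail that an article leaves to an analysis plan, and that plan is not shown. This stands. A reader might infer that the planned test is anti-conservative and its confidence interval too narrow; the document does not support that as a flat statement.

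A reader might also infer that the trial suffers inflated type I error and the t-quantile power loss together. It cannot. At design effect 1.36, an uncorrected test has about 6.4% type I error and keeps 79.6% power, while a corrected one holds 5% and has 76.0%.

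Nor should larger error rates be attached to this trial from stand-in models. Simulated null trials with 22 centres of 27 and 6.5% abstinence rejected 7.7% to 8.7% of the time with an uncorrected robust logit z-test, and 5.9% to 7.3% with a random-intercept logistic model. Neither is the planned survival model.

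Third, the small number of centres is not the main driver at the higher ICCs. At 0.05, normal-quantile power is already 57.3%, and the t quantile removes only about 4 points more. The protocol also gives 0.05 as a bound, not as its working value. Both remarks are fair, so 53% is the end of a range and not the expected power.

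None of this rescues the 80%. The mismatch between 20 and 27.5 per centre lies in the printed figures, lowers power even with normal quantiles at the implied ICC, and cannot be repaired by an analysis plan.

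**Conclusion.** The power statement is wrong as written. The 20 per centre, 22 centres and 604 patients cannot all hold. Taking 604 and 22 with the protocol's own 222 and implied ICC, power is about 76% with normal quantiles and about 72% with t(20). With t(20) it stays below 80% throughout the ICC range of 0.01 to 0.05. With normal quantiles it would exceed 80% only towards the low end of that range (82.8% at 0.01).

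The type I error part is conditional: about 6.4% instead of 5% if, and only if, the arm coefficient is referred to 1.96 without a small-sample correction.

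The figures rest on equal centres and 11 per arm, and on the two-proportion comparison used for the sample size, not on the planned survival model. They also take 222 as given. Because its control rate is not stated, a restated power is only as sound as that figure.

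**What to change.** 1. Reconcile the 20 per centre, the 22 centres and the total of 604, in the Sample size/power calculation section and the Discussion.
2. Restate the power for 22 centres of about 27.5 patients with t quantiles. State the ICC used, show a range such as the one above, and note that the result still depends on 222 and on a control rate that should be given.
3. Add one sentence to the Statistical analysis section: the arm coefficient and its confidence interval are referred to a t distribution with degrees of freedom equal to the number of centres, minus 2, minus the number of centre-level covariates. If an analysis plan already says this, point to it. A permutation test on centre-level abstinence proportions, within the randomisation strata, would be an optional check.

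The cost is a few sentences, a less favourable stated power and a slightly wider confidence interval. Restating the power requires no change to recruitment or treatment.
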